**4.2. Definition of an Adverse Event**

It is the responsibility of the investigators to ensure that all AEs, and other clinically significant findings that occur, are documented and accurately reported. It is important that all site staff understand the requirements and responsibilities related to safety reporting outlined below.

An AE is any untoward medical occurrence in a clinical investigation subject administered a product or medical device; the event need not necessarily have a causal relationship with the treatment or usage. Examples of AEs include but are not limited to:

- - Abnormal test findings
  - Clinically significant symptoms and signs
  - Changes in physical examination findings
  - Hypersensitivity
  - Progression/worsening of underlying disease
  - Additionally, they may include the signs or symptoms resulting from:
  - Drug overdose
  - Drug withdrawal
  - Drug abuse
  - Drug misuse
  - Drug interactions
  - Drug dependency

**4.3. Definition of a Serious Adverse Event**

A SAE or serious adverse drug reaction is any untoward medical occurrence at any dose that:

- - Results in death
  - Is life-threatening
  - Requires inpatient hospitalisation
  - Results in persistent or significant disability/incapacity
  - Results in congenital anomaly/birth defect

Medical and scientific judgment should be exercised in determining whether an event is an important medical event. An important medical event may not be immediately life threatening and/or result in death or hospitalisation. However, if it is determined that the event may jeopardise the subject and may require intervention to prevent one of the other AE outcomes, the important medical event should be reported as serious. Examples of such events include allergic broncho-spasm requiring intensive treatment in an emergency room or at home, blood dyscrasias or convulsions that do not result in hospitalization, or development of drug dependency or drug abuse.

Life-threatening refers to immediate risk of death as the event occurred per the reporter. A life-threatening experience does not include an experience, had it occurred in a more severe form, might have caused death, but as it actually occurred, did not create an immediate risk of death. For example, hepatitis that resolved without evidence of hepatic failure would not be considered life-threatening, even though hepatitis of a more severe nature can be fatal. Similarly, an allergic reaction resulting in angioedema of the face would not be life-threatening, even though angioedema of the larynx, allergic bronchospasm, or anaphylaxis can be fatal.

Hospitalisation is official admission to a hospital. Hospitalisation or prolongation of a hospitalisation constitutes criteria for an AE to be serious; however, it is not in itself considered a SAE. In the absence of an AE, a hospitalisation or prolongation of a hospitalisation should not be reported as an SAE. This is the case in the following situations:

- The hospitalisation or prolongation of hospitalisation is needed for a procedure required by the protocol.
- The hospitalisation or prolongation of hospitalisation is part of a routine procedure followed by the centre (eg, stent removal after surgery). This should be recorded in the medical record.

In addition, hospitalisation, for a pre-existing condition that has not worsened, does not constitute an SAE.

Disability is defined as a substantial disruption in a person’s ability to conduct normal life functions.

The relationship of the AE to Study Medication will be specified as follows:

1. Not related. In the investigators opinion, there is not a causal relationship between study medication and the AE.
2. Unlikely. Study medication is not likely to have any reasonable association with the AE.
3. Possibly. The AE could have been produced by the participant’s clinical state or study medication.
4. Probably. The AE follows a reasonable temporal sequence from the time of study medication administration and cannot be reasonably explained by the known characteristics of the clinical state.
5. Definitely. The AE follows a reasonable temporal sequence from the time of study medication administration.

AEs will be collected from the time of study drug administration through the follow-up period at 6 weeks post-study treatment. The investigators should attempt, if possible, to establish a diagnosis based on the presenting signs and symptoms. In such cases the diagnosis should be documented as the AE and not the individual sign/symptom. If a clear diagnosis cannot be established, each sign and symptom must be recorded individually.

The investigators should attempt to follow all unresolved AEs and/or SAEs observed during the study until they are resolved or judged medically stable, or are otherwise medically explained. If there is any doubt about whether the information constitutes a SAE, the information is treated as a SAE.

Certain information, although not considered an SAE, must also be recorded, reported, and followed up as indicated for an SAE. This includes:

- Overdose of an investigational product as specified in this protocol with or without an AE.
- Inadvertent or accidental exposure with or without an AE.

**4.4. Adverse Event Monitoring**

An independent study data monitoring committee consisting of between 3-4 Canterbury District Health Board specialist physicians will serve as the data and safety monitoring board for the study. A majority of the committee will have had prior experience in data/safety monitoring. [name], the study statistician will liaise with the committee and produce both open and closed reports for the committee meetings that will occur at least every six months. The committee will be notified within 24h of the investigators awareness of any SAE, and will be kept informed of the situation and its development on a continuing basis.

**5. STATISTICS**

**5.1. Sample Size**

The primary outcome measure is to compare the resolution of inflammatory infiltrate on a follow-up chest x-ray at 6 weeks post-study treatment between the vitamin D and placebo arms. These sample size calculations are based on an uncorrected chi square test. To detect an increase from 50% to 70% for clear chest x-rays and assuming an 80% retention rate, 180 participants per arm would be required for a power of 0.8. In addition, we aim to have a high proportion of deficient participants within the study cohort to increase the possibility of seeing an effect. We have calculated we will need to recruit ≈120 participants with deficient vitamin D levels at baseline (i.e. < 25 nmol/L). Thus, based on our previous findings and the data from the National Nutritional Survey^29^ up to 400 CAP patients may need to be recruited to get a sufficient number of deficient participants.

**5.2. Statistical Analysis**

All randomised participants will be included in the primary analysis. Data will be analysed on an intention to treat basis with dropout events reported on and examined for differential compliance between treatment and placebo arms. Primary analysis will be logistic regression of clear chest X-ray on treatment arm with covariates for age (grouped) and gender and if appropriate severity and comorbidities. Additional analyses will include covariates for initial 25OHD level and 25OHD level during the study and stratified analyses by 25OHD level at baseline; deficient (<25nm/l) and insufficient (<50nm/L). All data will be analysed in R (Vienna, Austria) or SAS (NC,USA).

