**1. SYNOPSIS**

| **Study Title** | Effect of adjunct high-dose vitamin D on community acquired pneumonia in hospitalised adults – a randomised controlled trial |
| --- | --- |
| **UTN** | U1111-1140-2885 |
| **ANZCTR No.** | ACTRN12613000582752 |
| **Trial Design** | Randomised, double blind, placebo-controlled trial |
| **Trial Participants** | Adults aged ≥ 18 years old, hospitalised with a confirmed radiological diagnosis of community acquired pneumonia |
| **Planned Sample Size** | up to 400 |
| **Follow-up duration** | 6 weeks post-study treatment |
| **Planned Trial Period** | June 2013-December 2014 |
| **Primary Objective** | To determine whether providing a single high-dose bolus of vitamin D as an adjunct treatment in adults hospitalised with community acquired pneumonia improves the resolution of pulmonary inflammatory infiltrate on chest x-ray compared with placebo. |
| **Secondary Objectives** | To determine whether providing a single high-dose bolus of vitamin D as an adjunct treatment in adults hospitalised with community acquired pneumonia improves patient outcomes compared with placebo. |
| **Primary Endpoint** | The resolution of pulmonary inflammatory infiltrate on a follow-up chest radiograph 6 weeks after taking study treatment. |
| **Secondary Endpoints** | Patient Outcome measures: Length of hospital stay; in hospital mortality; intensive care unit admission rates; amount and duration of antimicrobial therapy; rates of relapse and readmission to hospital after discharge; 6 week post-study treatment mortality rates; 12 month mortality rates; resolution of symptoms and return to normal activity based on participant questionnaire at 6 weeks post-study treatment. |
| **Investigational Medicinal Products** | Vitamin D_3_ |
| **Form** | Tablet |
| **Dose** | A single 200,000 IU, dose within 48 hours of admission to hospital with a confirmed radiological diagnosis of community acquired pneumonia. |
| **Route** | Oral |

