**3.3. Participants**

Participants will be recruited from CAP patients admitted to Christchurch Hospital and Princess Margret Hospital sites. On average, 400 to 500 people are admitted to these hospitals annually with a diagnosis of CAP, with the peak incidence occurring over the winter months (June to August).

Inclusion criteria:

1. A confirmed radiological diagnosis of pneumonia, defined as:

‘New inflammatory infiltrate on a chest radiograph where patients have an acute illness with clinical features of pneumonia and radiographic pulmonary shadowing that is at least segmental or present in one lobe and is neither pre-existing or because of some other known cause.’

1. <48 hours since admission to hospital
2. Age ≥ 18 years
3. Ability to give informed consent
4. Ability to orally consume the study medication
5. Ability to attend a follow-up appointment at 6 weeks post-study treatment for a chest x-ray

Exclusion criteria:

1. Pneumonia is not the principal reason for admission
2. Pneumonia associated with bronchial obstruction, bronchiectasis, or known tuberculosis
3. Use of vitamin D_3_ supplements other than as part of a multivitamin preparation where the daily intake would not exceed 400 IU.
4. High plasma corrected calcium > 2.6 mmol/L (corrected for plasma albumin concentration)
5. Use of immunosuppressants (e.g. doses of prednisone >10mg, methotrexate, azathioprine and cyclosporin)
6. Any prior history of hypercalcaemia, nephrolithiasis or sarcoidosis
7. Current kidney disorders requiring dialysis treatment or polycystic kidney disease
8. Cirrhosis of the liver
9. Women who are pregnant or are breastfeeding*
10. Already enrolled or planning to enrol in a research study that would conflict with full participation in the study or confound the observation or interpretation of the study findings (e.g. where vitamin D levels are tested and results are known by the participant; where the participant is required to take conflicting medications)

* At the 6 week follow-up women of reproductive age that think/know they are pregnant will also be excluded from taking further part in the study.

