**3.6.3. Assessment of Patient Outcomes**

Clinical data including basic demographics, routine haematological and biochemical information, length of hospital stay, in-hospital mortality, intensive care admission rates, amount and duration of antimicrobial therapy and rates of relapse and readmission to hospital and mortality rates at 6 weeks post-study treatment will be obtained from patient hospital records. For all participants, a CURB65 pneumonia severity score will be calculated from the clinical data collected. Research staff will also conduct a telephone interview with study participants at 6 weeks post-study treatment to complete a questionnaire regarding the resolution of symptoms and if the participants have returned to normal activity. Twelve-month mortality rates will be obtained from national databases.

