**3.7. Study Procedures**

**3.7.1. Recruitment of Participants**

All patients with a clincial diagnosis of pneumonia on admission to Christchurch Hospital are notified to a centralised patient registry which will be reviewed twice daily by members of the research team to identify potential participants. For these patients, computer records in the Depatment of Radiology will be selected electronically using an algorithm utilising key words such as pneumonia, consolidation and inflammatory infiltrate and the radiographs will be reviewed by a consultant radiologist to confirm the radiological findings. New admissions for CAP will be identified by study personnel on a daily basis on weekdays (Monday-Friday). Once identified, patients will be approached and asked to participate in the study within 48 hours of admission.

The study population will be comprised of at least the first 360 CAP patients that provide informed consent to participate (n= 180 per arm). However, to increase the possibility of seeing an effect, we aim to have ≈ 30% (n = 120) of the study cohort to be participants who are vitamin D deficient at baseline (25OHD levels <25 nmol/L). Thus, recruitment may need to continue to get the required numbers of deficient patients or until a maximum of 400 participants have been enrolled.

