**3.7.2. Baseline Visit**

The study will be explained to potential participants by trained research staff. After informed consent has been obtained and eligibility has been assessed, all participants will be provisionally enrolled in the study until the result of the corrected plasma calcium level is known. Only those patients that do not have hypercalcaemia (corrected plasma calcium > 2.6 mmol/L) will be fully enrolled and randomised to receive vitamin D_3_ or placebo. Clinical data (including basic demographics, biochemical measures and CURB65 severity score) will be obtained from the patients’ hospital records and confirmed as needed by patient enquiry. A blood sample for 25OHD measurement will also be obtained at baseline.

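### Extent of infiltrate on the admission film is neither recorded nor named as a covariate in the primary model; adding it would be a cheap, modest and optional gain in power

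*Protocol*

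**What the plan says.** The primary endpoint in the Synopsis is "The resolution of pulmonary inflammatory infiltrate on a follow-up chest radiograph 6 weeks after taking study treatment". Section 5.1 treats it as binary: "To detect an increase from 50% to 70% for clear chest x-rays".

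The model is set out in section 5.2: "Primary analysis will be logistic regression of clear chest X-ray on treatment arm with covariates for age (grouped) and gender". The covariate list in that sentence reads in full "covariates for age (grouped) and gender and if appropriate severity and comorbidities". Age group and gender are therefore fixed, and severity and comorbidities are conditional. Neither conditional term is defined in that section.

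The only severity measure defined elsewhere is clinical. Section 3.6.3 states "For all participants, a CURB65 pneumonia severity score will be calculated from the clinical data collected", and section 3.7.2 states "Clinical data (including basic demographics, biochemical measures and CURB65 severity score) will be obtained from the patients’ hospital records". Neither list contains a radiographic item.

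On the admission film, eligibility in section 3.3 asks for "radiographic pulmonary shadowing that is at least segmental or present in one lobe", which sets a minimum. Section 3.7.1 says that "the radiographs will be reviewed by a consultant radiologist to confirm the radiological findings". No section says that extent is graded or entered as data.

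**The concern.** Participants enter with different amounts of shadowing to clear: the eligibility rule sets a floor and no ceiling. Section 3.7.3 describes block randomisation and states no stratification, so the analysis model is the one place left where extent could be taken into account. On the Protocol's own definitions the conditional severity term points to CURB65, which is calculated from clinical data and not said to include the film.

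What is at stake is efficiency. If extent predicts clearance, leaving it out gives up some power. That matters little at the planned 20-point difference. It matters more if the true effect is nearer the differences in the unpublished cohort in section 2.3.3, where complete resolution was 67% above 50 nmol/L, 56% at 25-50 nmol/L and 53% below 25 nmol/L. Those are observational contrasts between 25OHD groups, used here only as a scale for smaller effects.

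**Working it through.** **Inputs from the Protocol.** Clear films 50% versus 70%, 180 per arm, 80% retention, power 0.8, uncorrected chi-square (5.1); 1:1 allocation (3.7.3); cohort clearance 53%, 56% and 67% (2.3.3). Section 5.1 does not state alpha; two-sided 0.05 is assumed.

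**Inputs that are assumed.** More than one lobe involved in 30-40% of participants; odds ratio for clearance, more than one lobe versus one segment or lobe, of 0.5 to 0.2. The documents give neither.

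**Step 1: the Protocol's own figure.** With mean proportion 0.6,

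n = [1.96 × √(2 × 0.6 × 0.4) + 0.8416 × √(0.5 × 0.5 + 0.7 × 0.3)]² / 0.2² = (1.358 + 0.571)² / 0.04 = 93 evaluable per arm,

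and 93 / 0.8 gives 117 recruited. The stated 180 per arm is not reproduced. Working forward, 180 × 0.8 = 144 evaluable, and power is Φ[(0.2 × √144 − 1.358) / 0.678] = Φ(1.54) = 0.938. That mismatch is a separate matter. It is relevant here only because it leaves little room for improvement at 50% versus 70%.

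**Step 2: power without extent, 144 per arm, same formula.** 50% versus 70%: 93.8%. 53% versus 67%: 68.1%. 56% versus 67%: 48.3%.

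**Step 3: power with a binary extent term.** 4,000 simulated trials per setting, logistic Wald test, with intercept and treatment effect solved so that the marginal clearance rates stay as stated. The ranges run over the assumed prevalences and odds ratios.

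| Clearance | Without extent | With extent |
|---|---|---|
| 50% vs 70% | 93-94% | 94-96% |
| 53% vs 67% | 67-69% | 70-75% |
| 56% vs 67% | 46-48% | 47-53% |

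Simulation error is about √(0.7 × 0.3 / 4000) = 0.7 points on a power near 70%, so the smallest gains are barely distinguishable from zero.

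**Step 4: sensitivity to the assumed strength.** Prevalence 30%, 144 per arm, 50% versus 70%:

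| Odds ratio for extent | Without | With |
|---|---|---|
| 1 | 93.8% | 93.8% |
| 0.6 | 93.2% | 93.4% |
| 0.4 | 93.1% | 94.3% |
| 0.25 | 93.4% | 95.4% |
| 0.15 | 93.5% | 96.9% |

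With 93 per arm at 50% versus 70%, or 144 per arm at 50% versus 66%, where unadjusted power is about 79-80%, the gain over the same odds ratios runs from 0 to about 7 points. It is 1-2 points for odds ratios of 0.6 to 0.4.

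**Step 5: where the gain comes from.** The marginal odds ratio is (0.7/0.3) / (0.5/0.5) = 2.33. Conditional on extent with odds ratio 0.15 it is 2.77. In logistic regression the power comes mainly from this larger conditional effect and not from a smaller standard error.

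**Step 6: size of a chance imbalance.** With 35% having more than one lobe involved, the between-arm difference in that share has standard deviation √(2 × 0.35 × 0.65 / 144) = 5.6 points, so two standard deviations is 11.2 points. At 60% overall clearance, an odds ratio of 0.5 means about 66% versus 49% by extent (17 points), and 0.2 means about 73% versus 35% (38 points). The shift in the clearance difference is then 0.112 × 17 = 1.9 to 0.112 × 38 = 4.3 points, against an effect of 11-14 points on the cohort scale.

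**The case against.** The case against is strong on several counts.

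- **The model is not closed at age and gender.** A reader of the first half of the sentence in 5.2 might infer that it is. The sentence goes on to admit severity and comorbidities, and severity could be read to include the film. This stands, but the clause is conditional and does not fix extent in the model.
- **Covariate choice is often left to the analysis plan**, which is not shown. This stands in part. However, the Protocol itself names the primary covariates and lists the baseline data, and a covariate that is not collected cannot be adjusted for.
- **Extent is not the baseline value of the outcome.** A reader might call it that. The endpoint is clear or not clear, and everyone is not clear at entry by eligibility, so the baseline value is constant. Extent is a candidate prognostic factor and no more.
- **Extent is not shown to exist as data.** A reader might infer from sections 3.3 and 3.7.1 that it is already graded and free to use. The review confirms findings against a minimum; a field would have to be defined and filled in.
- **Imbalance is not bias.** The shift in step 6 is random error, already covered by the confidence interval and the type I error rate under randomisation.
- **The size is assumed.** The larger gains need a strong predictor, which nothing in the documents supports. The simulation also compares models with and without extent alone; beyond age, gender and possibly CURB65, the increment would be smaller if these overlap with extent. Nor should the gain be read as a saving in participants from explained variance, which is a linear-model argument.

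What remains is that a plausible, cheaply recorded prognostic factor is left out.

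**Conclusion.** The point holds as a modest improvement. The primary model fixes age group and gender and leaves severity optional; extent of the admission infiltrate is neither collected as a data item nor named as a covariate.

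Under the assumed prevalence of 30-40% and odds ratios of 0.5 to 0.2, with 144 evaluable per arm, prespecifying extent would add about 1-3 points of power at 50% versus 70% and about 1-6 points at 53% or 56% versus 67%. With a weak predictor the gain is close to nothing, and if extent is unrelated to clearance there is no meaningful loss. The documents cannot narrow this range.

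The documents do not support a reading that the planned analysis is invalid, biased or underpowered because of this omission: at the planned effect and retention, power is already about 94%.

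**What to change.** At the point where the radiologist confirms the admission film, before allocation, record whether the infiltrate involves one segment or lobe, or more than one lobe. Add this item to the baseline data in section 3.7.2. In section 5.2, name it as a fixed covariate of the primary logistic model beside age group and gender, so that its inclusion does not depend on a later judgement.

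The cost is one field on the form, one term in the model and one degree of freedom. No additional film or reader is needed.

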**2.2.3. Vitamin D Levels and New Zealand**

Even if the 50 nmol/L cut-off is used to define sufficiency, low vitamin D levels are common world-wide^28^. Vitamin D levels in the New Zealand general population are, on average, lower than at similar latitudes elsewhere in the world. Results from the 2008 New Zealand Adult National Nutritional survey show that just over 27.1% of the population (25.2% men and 28.5% women) have insufficient levels (<50 nmol/L) and nearly 5% are frankly deficient (<25 nmol/L). 25OHD levels are lower in Māori (33.7% insufficient, 6% deficient) and Pacific People (46.6% insufficient, 10.5% deficient) than other ethnic groups. Pacific women have the worst vitamin D status with a reported mean 25OHD concentration of 46.0 nmol/L and over half (53.2%) have insufficient levels. For all adults, mean 25OHD levels are lower in the Southern region compared with Northern or Central parts of New Zealand throughout the year. This is most pronounced over the late winter and early spring months (August-October), where mean levels are 45.5 nmol/L for the Southern region compared with 56.1 nmol/L and 50.5 nmol/L in Northern and Central regions respectively^29^. A Christchurch study demonstrated that most, if not all, of 201 apparently healthy adults randomly selected from the electoral roll did not have adequate circulating 25OHD at some time in the year. Even in February, when UVB exposure is high, only 12% had plasma levels >80 nmol/L^30^. Similarly, a study of over 400 adult CAP patients admitted to either Christchurch (n=300) or Waikato Hospitals (n=123) were found to have median 25OHD levels of 30 nmol/L (28 nmol/L for Christchurch patients and 34 nmol/L for Waikato patients) and 26% exhibited severe deficiency with levels ≤ 20 nmol/L (unpublished).

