Since the 1930’s it has been assumed that vitamin D_2_ and vitamin D_3_ have the same efficacy in raising 25OHD concentrations, but recent data has questioned the validity of this assumption. Of the limited evidence currently available, it appears that vitamin D_2_ is less efficacious than vitamin D_3_ when given in large monthly or single bolus doses^36-38^, yet when either form of the vitamin is given in smaller daily doses, circulating 25OHD levels increase to the same degree^36^. Studies have shown that following a single large bolus dose (50,000, 100,000 or 300,000 IU) of either vitamin D_2_ or D_3_ there is a similar rapid and significant rise in 25OHD concentrations over the first 3 days, indicating equivalent absorption. After which, 25OHD levels continue to rise following vitamin D_3_ supplementation, peaking between 7 and 14 days before declining, with it taking >60 days for 25OHD levels to return to pre-supplementation levels^37,39^. However, following vitamin D_2_ supplementation, 25OHD concentrations fall rapidly after 3 days and are not significantly different from pre-supplementation levels at 14 days^36-38^. The same pattern is observed when vitamin D_2_ or D_3_ is provided intramuscularly, with a single large dose of vitamin D_3_ being almost twice as potent as D_2,_ however, the rise in 25OHD concentrations is far greater for both forms of the vitamin when given orally^38^.

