Observational studies of vitamin D and respiratory infection are likely to be affected by biases in measurement of both the relevant vitamin D level and the outcome, as well as potential confounding by exposure to sunlight (e.g. ‘sickly’ children might be less likely to spend time uncovered outside). Strong evidence of whether there is an effect of vitamin D on the risk of infection can be generated only by randomised controlled trials.

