**3.4. Intervention**

Participants randomised to the active treatment will receive a single oral dose of 200,000 IU vitamin D_3_ < 48 hours of admission to hospital with a confirmed radiological diagnosis of CAP. Those randomised to placebo will receive matching inactive tablets that will be administered in an identical regimen. The vitamin D_3_ and matching placebo tablets will be sourced from Tishcon Corp (an accredited pharmaceutical company in New Jersey, USA). All treatments will be directly administered to participants by research staff upon enrolment into the study.

The dose of 200,000 IU vitamin D was chosen to rapidly increase serum 25OHD levels to approximately 80-100 nmol/L and is based on data from two studies that have assessed the pharmacokinetics and safety of high dose vitamin D_3_. One study in healthy adults showed that a single oral dose of 100,000 IU vitamin D_3_ increased plasma 25OHD levels from around 65 nmol/L to ≥ 80 nmol/L within 24 hours and reached a maximum of approximately 100 nmol/L at 7 days following consumption^39^. A second study in elderly women showed that a single oral dose of 300,000 IU sharply increased 25OHD levels from approximately 30 nmol/L to 125 nmol/L after 3 days and levels reached a maximum of approximately 150 nmol/L within 30 days of consumption before decreasing^38^. There were no safety issues or incidences of hypercalcaemia reported for either study. Similarly, two further studies that used single large bolus doses of 500,000 IU vitamin D showed that 25OHD levels were between 150-210 nmol/L one month following supplementation and neither study reported any incidences of hypercalcaemia^91,92^. Thus, large single doses of vitamin D_3_ up to 500,000 IU have been shown to be safe and effective for rapidly raising 25OHD levels above 80 nmol/L.

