**3.6.2. Blood Tests**

Blood samples will be collected at recruitment and at 6 weeks (± 1 week) after receiving study treatment and will be stored. Vitamin D (25OHD) levels will be measured on baseline blood samples at the end of the 6 week follow-up period to assess the proportion of people recruited into the study with deficient levels (<25 nmol/L). These baseline measures will be fed-back to the participant’s GP who will be responsible for the on-going care of the participant. The final blood sample collected at the end of the 6 week post- study treatment follow-up period will be stored and 25OHD levels measured after all participants have completed the 6 week follow-up period so as not to compromise the blinding of participants or research personnel. Plasma calcium and albumin levels will be measured in real-time on all samples collected and the corrected plasma calcium (i.e. corrected for plasma albumin concentration, as is standard laboratory practice) will be reported in order to check for hypercalcaemia (an elevated plasma corrected calcium is > 2.6 mmol/L). Only the corrected plasma calcium levels will be made available to investigators before the end of the 6 week follow-up period.

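### An additional analysis in Section 5.2 adjusts for week-6 25OHD, a post-dose value on the hypothesised causal path, so its arm coefficient does not estimate the treatment effect

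*Protocol*

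**What the plan says.** Protocol Section 5.2 sets the main model first: "Primary analysis will be logistic regression of clear chest X-ray on treatment arm with covariates for age (grouped) and gender", with severity and comorbidities added if appropriate. 25OHD is not in that model. The section then says: "Additional analyses will include covariates for initial 25OHD level and 25OHD level during the study", and adds analyses stratified by baseline 25OHD. It gives no purpose, estimand or caution for the model with the during-study level.

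Section 3.6.2 fixes when 25OHD can be known: "Blood samples will be collected at recruitment and at 6 weeks (± 1 week) after receiving study treatment and will be stored". On the second draw it says: "The final blood sample collected at the end of the 6 week post- study treatment follow-up period will be stored and 25OHD levels measured", once all participants have finished follow-up. Section 3.7.4 places that draw at the same time point as the outcome chest x-ray.

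Section 3.4 says what the treatment is for: "The dose of 200,000 IU vitamin D was chosen to rapidly increase serum 25OHD levels to approximately 80-100 nmol/L".

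**The concern.** A covariate used to sharpen or balance a randomised comparison should not itself be affected by treatment. Baseline 25OHD meets that condition. Week-6 25OHD does not, because the dose was chosen to change it.

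Conditioning on it does two things. It blocks whatever part of the effect passes through 25OHD as measured at week 6. It also compares treated and placebo patients who ended at the same level, and they may differ in other ways that randomisation had balanced. A treated patient who reaches only a typical placebo level may be frailer or absorb poorly.

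At stake is how a prespecified adjusted odds ratio would be read beside the primary one. A real benefit could look as if it vanishes on adjustment, or an inert treatment could look harmful.

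**Working it through.** **Which 25OHD value is it?** There are two draws, at recruitment and at week 6 (42 ± 7 days, so days 35–49). The first is the initial level, so the during-study level can only be the second.

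**Do the arms still differ then?** Section 2.2.4 says of a D3 bolus, "with it taking >60 days for 25OHD levels to return to pre-supplementation levels". Days 35–49 fall before day 60, so a difference should remain. A similar local pneumonia cohort (Section 2.2.3) "were found to have median 25OHD levels of 30 nmol/L". Against the 80–100 nmol/L target, that implies an intended early rise of 80 − 30 = 50 to 100 − 30 = 70 nmol/L. The protocol gives no expected week-6 level, so rises of 25 and 45 nmol/L are assumed below.

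**Inputs.** The protocol has no figure for this model to reproduce. From Section 5.1: 180 per arm × 0.80 retention = 144 per arm analysed, and clear x-rays in 50% versus 70%. Assumed, not from the protocol: baseline 25OHD mean 33, SD 15; SD of the rise 15; other week-6 variation SD 8; two-sided 5% tests.

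**Attenuation.** Let the effect run wholly through the week-6 level W, with logit P(clear) = b(W − 33) and b = ln(0.7/0.3)/rise = 0.847/rise. The total arm effect is about b × rise = 0.847. With W held fixed nothing is left, so the arm coefficient is 0. If a share m of the effect passes through W, about (1 − m) remains: at m = 0.5, 0.8 × 0.5 = 0.4.

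**Standard error.** Given baseline, the within-arm variance of W is 8² = 64 on placebo and 64 + 15² = 289 on active, mean 176.5. Variance inflation = 1 + rise²/(4 × 176.5).
- Rise 25: 1 + 156.25/176.5 = 1.885; square root 1.37; 0.254 × 1.37 = 0.35.
- Rise 45: 1 + 506.25/176.5 = 3.868; square root 1.97; 0.251 × 1.97 = 0.49.

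**Spurious effect under the null.** Let an unmeasured factor lower W by 10 nmol/L and the log odds of clearance by 0.8 per SD. Within-arm variances become 164 and 389, mean 276.5. The induced slope on W is about 0.8 × 10/276.5 = 0.0289 per nmol/L, so the arm coefficient is about −0.0289 × rise: −0.72 at rise 25 and −1.30 at rise 45.

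**Simulation** (1,000 trials per row; both models contain arm and baseline 25OHD). Cells give mean log OR / mean SE / proportion with p < 0.05.

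| Scenario | Rise | Without week-6 25OHD | With week-6 25OHD |
|---|---|---|---|
| Wholly mediated effect | 25 | 0.81 / 0.25 / 0.90 | −0.01 / 0.36 / 0.06 |
| Wholly mediated effect | 45 | 0.83 / 0.25 / 0.93 | 0.00 / 0.50 / 0.04 |
| No effect, no common cause | 25 | 0.00 / 0.24 / 0.05 | 0.00 / 0.34 / 0.04 |
| No effect, no common cause | 45 | 0.00 / 0.24 / 0.05 | −0.02 / 0.48 / 0.04 |
| No effect, common cause | 25 | 0.00 / 0.24 / 0.04 | −0.70 / 0.31 / 0.62 |
| No effect, common cause | 45 | 0.00 / 0.24 / 0.04 | −1.22 / 0.43 / 0.84 |

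In the last two rows, every significant result with week-6 25OHD points to harm (median OR 0.49 and 0.30). The hand calculations agree closely with the simulation.

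**Sensitivity to the assumed factor.** In a variant the factor also lowers baseline 25OHD, baseline and week-6 residuals correlate at 0.6, and the factor is worth 8–10 nmol/L and 0.5–0.8 log odds per SD. At a week-6 separation of 45 nmol/L the false-positive rate is about 18–48% with the week-6 level alone, but about 8–17% once baseline 25OHD is included, as Section 5.2 plans. At a separation of 20 it is about 6–10%. Other settings with baseline included gave about 8–59%.

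**The case against.** The clause concerns additional analyses only. A reader might infer that the trial's main treatment comparison is biased. It is not: the primary model in Section 5.2 contains no 25OHD term.

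The protocol also does not say that this model is meant to estimate the treatment effect. Adding the achieved level and watching the arm coefficient shrink is a familiar, if crude, look at mechanism, and a statistical analysis plan may label it so. That stands as a possible intent. However, the protocol itself commits to the covariate without such a purpose, and a plain covariate model supports a mediation reading only under further assumptions.

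It is also tempting to say that adjustment removes the effect. That needs the whole effect to pass through the week-6 value. Section 2.2.4 has levels peaking at 7–14 days and then declining, so week 6 is a late proxy for early exposure, and partial attenuation is at least as plausible.

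Nor is spurious harm a certainty. It needs an unmeasured common cause, and without one the test keeps its size. The protocol does make one plausible. Section 2.3.3 reports complete resolution in 67% of patients above 50 nmol/L against 53% below 25 nmol/L, and warns of bias in observational studies "as well as potential confounding by exposure to sunlight". That does not establish a common cause in this trial, or its strength.

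Finally, the model loses participants without a week-6 sample. Since the x-ray is due at the same time point, most of them would lack the outcome too, so this adds little.

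**Conclusion.** The point holds for one covariate in an additional analysis. The direction of the problem follows from the protocol alone: the value is post-dose, the dose is meant to raise it, and the arms should still differ at week 6. The arm coefficient from that model is therefore not an estimate of the treatment effect.

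The size rests on assumed inputs. The log OR goes from about 0.8 to about 0 under full mediation and to about 0.4 under half mediation, and the SE rises from about 0.25 to about 0.3–0.5. Null rejection is about 4–5% without a common cause. With one it is roughly 8–59%, falling to 6% at the smallest separation tried and reaching 84% with the strongest factor. That spread shows that no single false-positive rate can be quoted as a property of this trial.

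The primary analysis, the baseline 25OHD covariate and the baseline-stratified analyses are sound on this point. Severity is moderate: wrong as written, but confined to supporting analyses.

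**What to change.** In Section 5.2, strike the during-study 25OHD level from every model that estimates the treatment effect, and keep the baseline level. Possible wording: *Additional models will adjust for baseline 25OHD. Week-6 25OHD will be summarised by arm as a measure of achieved exposure and will not be a covariate in any model used to estimate the effect of treatment.*

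If the investigators want a model that contains week-6 25OHD, keep it under its own heading as an exploratory mediation or exposure-response analysis. State its assumptions, in particular that week-6 25OHD and clearance share no unmeasured cause if it is a mediation model, and say that its arm coefficient is not a treatment-effect estimate.

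The cost is one clause or one added sentence. No new data, visits or participants are needed, and the primary analysis does not change.
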